### 3. Purpose:

School gardening programs offer affordable and accessible fruits and vegetables (FV), teach children how to grow, cook, and enjoy FV, and show promising effects on reducing obesity and related diseases in low-income Hispanics. Lack of access to healthy and affordable food is a significant factor contributing to elevated rates of obesity and metabolic risk factors among low-income Hispanics. There is a growing national and grassroots movement to support gardening efforts to make healthy foods more affordable and accessible and to make intake more sustainable for low-income families. However, few experimental studies have evaluated the impact of garden-based interventions on obesity and related metabolic disorders.

The overall goal of this project is to test the effects of a large school-based gardening, nutrition, and cooking randomized control trial (called "TX Sprouts") on dietary intake, dietary-related behaviors, obesity, and related metabolic disorders in low-income Hispanic youth and their families in Central Texas. Elementary schools will be randomized to either: 1) TX Sprouts intervention or 2) Control (delayed intervention). At each intervention school, we will build edible gardens; form and train Garden Leadership Coalitions (GLCs); teach 20 TX Sprouts in-school lessons to the students; and teach nine family-based TX Sprouts lessons throughout school year.

After the intervention year, we will provide a series of training workshops and resources to the GLCs and schoolteachers to sustain the TX Sprouts program in subsequent years. We will measure the sustainability employed by each school by process logs/surveys, structured interviews, surveys and school observations. The findings could provide a successful, sustainable model for garden-based school programs that decrease the obesity and metabolic diseases impacting Hispanic populations.

All participating school will get the TX Sprouts program regardless, because it is taught during school hours. This research study is to be allowed to conduct evaluation measures. The related consent forms pertain to the research/evaluation portion of this proposal.

**Aim 1:** To test the effect of the Sprouts intervention on the following changes in health outcomes for the child: a) FV intake; b) dietary psychosocial variables; c) anthropometric parameters (e.g., BMI, WC, percent body fat); d) metabolic risk factors (e.g., blood pressure, metabolic syndrome, fasting glucose, insulin, and lipids); and e) home environment (e.g., availability and accessibility of FV).

***Hypothesis 1:*** Sprouts intervention students compared to control students will have, as primary outcomes: increased vegetable intake and reduced BMI z-scores, WC, fasting glucose, and insulin; and, as secondary outcomes: increased fruit and fiber intake and reduced added sugar intake, improved dietary psychosocial variables (i.e., preference and motivation, self-efficacy for FV), and reduced body fat and other metabolic risk factors.

**Aim 2:** To test the effects of the TX Sprouts intervention on changes in dietary intake and related dietary psychosocial variables of the parents.

**Hypothesis 2:** TX Sprouts intervention parents compared to control parents will have increased FV intake, improved psychosocial variables linked to FV intake, and improved access and availability of FV in the home.

**Exploratory Aim:** To identify specific strategies/components of the TX Sprouts intervention that were implemented and sustained at the completion of the intervention, which will provide valuable information on how to disseminate and sustain long-term garden programs in schools.

#### 4. Procedures:

##### **TX Sprouts Program:**

Sixteen elementary schools (~4,800 3rd-5th grade students) from four independent school districts have been identified with: a) >50% Hispanic children; b) >50% participation in the free/reduced school lunch program; c) located within 60 miles of the University of Texas at Austin campus; d) high prevalence of pediatric obesity; and e) interest in a school garden/nutrition program. Elementary schools will be randomized into either: 1) TX Sprouts Intervention or 2) Control (delayed intervention). At each intervention school, we will build edible gardens; form and train Garden Leadership Coalitions (GLCs); teach 20 TX Sprouts in-school lessons to the students; and teach nine family-based TX Sprouts lessons throughout school year. The control schools will serve as the comparison group and will receive a delayed intervention the next year.

**Garden Leadership Coalition (GLC):** We will establish GLCs at each of the schools during the intervention phase, which will facilitate some of the school-level components of the intervention. These GLCs will be comprised of interested teachers, school staff, senior citizens, parents, and children, but these groups will be different and unique at each school site. . Given that the CATCH program is currently being implemented in all participating school districts as the state-mandated coordinated school health programs, we will enlist the CATCH Champions and Wellness Committees at each school to be a part of the GLC. Key personnel (Drs. [name], [name], [name], and [name]) have considerable experience with coalition building in schools. We will employ a GLC Coordinator to help form and organize GLCs at each school site and serve as the liaison between the GLCs and the Sustainable Food Center (SFC), a nationally recognized Austin-based non-profit organization that promotes gardening and health eating in a culturally relevant manner. SFC has developed and currently teaches School Garden Leadership Trainings across the Austin area. SFC will host a Garden Leadership Training workshop during the intervention phase and will then teach a series of three workshops to the GLCs in the subsequent year. Currently, SFC offers several workshops, including: Basic Organic Gardening classes (which includes information on planting fruit trees, rain water collection, fence building, and gardening in pots/containers), Farm Direct classes (which connect local growers with schools), and La Cocina Alegre (a series of family cooking classes using fresh produce). The GLC Coordinator will work with the GLCs to select and provide these workshops to the schools; the cost of the workshops will be covered by this grant. The grant will also pay for an AgriLife Extension Coordinator to help provide local Master Gardener volunteers to work with the GLCs to help maintain the gardens and sustain the gardening program. As part of the Extension Master Gardener program, all volunteers undergo a 3-month training program and then must complete 50 hours of volunteer work the first year and 30 hours of volunteer work every year after, so this partnership is ideal for their program as well as the school sites. The GLC coordinator, the Extension Coordinator, and the Master Gardener volunteers will continually help connect the GLCs to local stakeholders, including local agricultural producers, community gardens, food pantries, food banks, and senior citizen centers. GLCs will be encouraged to meet before or after school twice a month in the beginning and at least monthly for the remaining years. The GLCs will be responsible for holding design-build meetings and for planning and implementing the Garden Kick-Off and Harvest Celebration events. GLCs will develop an action plan to engage school maintenance staff, teachers, and other community members to get involved in the program as well as reach out to garden sponsors and local foundations to fundraise in subsequent years. Other potential strategies that the GLC might employ include: hosting family plant and harvest days throughout

the year, hosting community engagement demonstrations, (i.e., FV stands, farmer's markets, and recipe demonstrations), and contacting local media outlets to do stories on garden activities/program. Of note, every GLC will likely implement and adapt different strategies from a menu of evidence-based options, which is why we plan to develop a list of these options, and measure these strategies in both intervention and sustainability years as done in the CATCH Travis County study. Forming these GLCs will empower the community members to take ownership in this program and continue to maintain the gardens and sustain the program after the grant cycle is over.

**Edible Gardens:** We have support from school districts and the individual schools to build gardens at each of the school sites. Raised beds will be used at all garden sites, as these are easy to build, make garden access easy for children of all developmental levels, ensure that soils are free of heavy metals/contaminants, and reduce weeds in the garden area. We have support from school districts and the individual schools to build gardens at each of the school sites. Raised beds will be used at all garden sites, as these are easy to build, make garden access easy for children of all developmental levels, ensure that soils are free of heavy metals/contaminants, and reduce weeds in the garden area. The beds will be designed by the GLCs at each school during a “design-build” session with input from the maintenance staff and principals as well as assistance from Texas AgriLife Extension staff and the SFC. Supplies will be purchased from this grant, with the local horticulturist's guidance, and delivered to the appropriate garden site. A garden kick-off event at each garden site will engage students, teachers, practitioners, parents, and community volunteers in a garden build. Each school site will get the materials and supplies needed for garden upkeep (e.g. rakes, hoses, etc.) and for teaching the lessons, (e.g., tables, chairs/benches, cooking grill, portable hand-washing sink, pots/pans, etc.). A big media/kick-off event will be hosted at each school after each garden is built. In addition, the Extension Volunteer Coordinator will place and oversee Master Gardener volunteers who live within each of these communities to assist with the build and upkeep of the garden in the intervention year, as well as subsequent years

**Curriculum:** We will use an adapted version of the LA Sprouts curriculum. LA Sprouts includes 12 lessons, each approximately 90 minutes in length), and we will break it down to 20 lessons, each 30-45 minutes in length taught during intervention year of this project. The following nutrition topics are included in the curriculum: a) healthy cooking/preparation of FV (i.e., low in sugar and fat); b) FV preservation; c) eating locally produced food; d) low-sugar beverages made with fresh FV; e) health benefits of FV; f) how to eat healthfully in food desert neighborhoods; and g) food equity and community service. The curriculum also covers a broad range of horticultural and environmental education topics including: science process skills, observation, taking measurements, and problem solving through both group and individual learning experiences. The curriculum is culturally tailored to Hispanics, including culturally appropriate recipes, content, and activities. In addition, Extension materials and the SFC programs are available in Spanish and are culturally appropriate. The curriculum is mapped on Texas Essential Knowledge and Skills (TEKS) standards for science, math, language arts, health, and social studies.

For the parent lessons, we will use the developed and tested LA Sprouts family curriculum that parallels the nutrition and gardening topics/activities taught to the children. The LA Sprouts family curriculum includes twelve 90-minute lessons, which will be divided into nine 60-minute lessons for the proposed project. The parent curriculum is available in both English and Spanish and has been culturally adapted and evaluated. The curriculum has a strong emphasis on the cooking components and focuses on growing and cooking foods that are culturally appropriate. Often, the children are given the opportunity to teach their parents how to cook healthy meals with FV. This model empowers the child to be the champion for healthy changes in the family. Some of the more popular activities in this curriculum include: family cooking competitions, recipe development and sharing, and fall/spring harvest celebrations.

**School Lessons:** All 3rd-5th-grade students in the participating schools will receive the curriculum as part of their normal school day. We will hire bilingual nutrition and garden educators who have experience teaching nutrition/ gardening programs to teach the TX Sprouts curriculum in the Intervention year. All educators will undergo a weeklong training course led by the research and Extension staff that will cover all material/activities taught during each lesson, structure and flow of each class, cooking and preparation

skills needed to make recipes in curriculum, classroom preparation/clean up procedures, logistical issues with teaching in garden, how to complete process logs, and any issues with supervising student volunteers. The schoolteachers will “shadow” our educators during these lessons the first year. Twenty TX Sprouts lessons (each 30-45 minutes in length) will be taught by our educators separately to each 3rd-5th grade classroom throughout the school year as part of their normal school day. Before the program is implemented, we will work with stakeholders in each school district to decide exactly where and when these lessons can be taught and incorporated into normal school days.

***Family Lessons at Schools:*** The bilingual garden/nutrition educators will also teach monthly TX Sprouts lessons throughout the school year for the families of participants at each of the schools, for a total of nine lessons. Each lesson will be taught by a bilingual gardening/nutrition educator and will consist of a 60-minute lesson that parallels the topics taught during the student lessons. We will incentivize the parents to attend the lessons by offering free meals, produce, groceries, and free babysitting for younger siblings.

***Delayed Intervention to Control Schools:*** The control schools will receive a delayed intervention (identical intervention as described above) in the year after the post-testing for that wave. Baseline and post-intervention measurements will occur in the control parents and students within the same time period as the intervention schools. Every control school will receive a garden, identical in size and structure to the intervention schools. We will teach school lessons as well as offer monthly family lessons at the schools. We have used the delayed intervention control group in the past with success, and it provides incentives for families and schools to stay involved in the study as in the control group

### **TX Sprouts Research Evaluation:**

Evaluation measures will be collected at baseline and end of the school year in both treatments (intervention and control schools). Measurements will occur during the first four weeks of school in the fall and the last four weeks of school in the spring. Most measures on children will be collected at the schools during normal school hours. The fasting blood draws will occur first thing in the morning before school starts. The following evaluation measures will be obtained from students at baseline and post-intervention:

- Measured height, weight, BMI parameters, waist circumference (WC), body composition (via bioimpedance); carotenoid scan of skin
- Blood pressure via child-specific automated cuff;
- Subsample of students will complete three 24-hour diet recalls by telephone;
- Child survey assessing dietary intake via food screener and related determinants of dietary behaviors (e.g., preference/motivation/self-efficacy to eat FV);
- Program lessons may also be audio/visual recorded;
- Voluntary fasting blood sample to assess glucose, insulin, and lipid parameters;
- Accelerometers to measure physical activity;
- Time on Task observations

Parent questionnaires will be handed out or mailed to the homes after consent is obtained at baseline and post-intervention. Questionnaires are translated into Spanish, culturally appropriate, and take ~60 minutes to complete. We will encourage parents to complete the questionnaire before the first family lesson and return it via mail (pre-paid postage will be provided). However, parents will also be able to complete the questionnaire at the first and last lessons. Parent surveys will evaluate the following: food security via USDA validated questions, confidence cooking, dietary intake via validated screener, reported height and weight, medical history, basic demographics, child feeding practices and food home environment from CEBQ and TGEQ, and preferences adapted from Domel et al. We will also attempt to measure height and weight on a subsample of parents, which will occur at the first and last parent lesson. Parent workshops may also be audio/visually recorded.

After the intervention year, we will conduct a series of structured interviews (30 minutes or less per interview) as well as surveys, with participating school stakeholders (i.e., principals, teachers,

administration staff) and members of the GLCs to measure sustainability approaches employed at each school. We will audio recorded these structured interviews. We will provide a sustainability consent form for participants to sign prior to agreeing to the interview. We will also conduct in-school observations to document sustainability measures around the TX Sprouts program.

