## 5. Measures

**Anthropometrics, Body Fat, and Blood Pressure:** For both children and parents, weight will be measured using a SECA (model 869) digital scale to the nearest 0.1 kg, and height will be measured using a wall-mounted stadiometer to the nearest 0.1 cm. BMI ( $\text{kg/m}^2$ ) and BMI percentiles for CDC age- and gender-specific values will be determined using EpiInfo 2005, (CDC, Atlanta, GA). Waist circumferences (WC) will be measured and recorded to the nearest 0.1 cm. Body composition will be assessed using Bioelectrical Impedance with the Tanita Body Fat Analyzer (model TBF 300). Blood pressure will be obtained in duplicate with an automatic cuff according to recommendations of the American Heart Association. A skin carotenoid scan will be completed of the finger, which will take approximately 20 seconds. This is a noninvasive device that measures carotenoids in the skin to assess fruit and vegetable consumption. The device uses a technique called reflectance spectroscopy, which involves shining a light on the skin of one finger to measure carotenoids in the skin which gives us an objective measures of vegetable intake.

Parental height, weight, body fat, WC, and blood pressure will be collected at first and last family workshop (expecting a subsample only). Therefore we will ask self-reported height and weight in questionnaire packets.

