## **8. Compensation**

A subsample of children will complete three 24-hour diet recalls and we will provide any child that completes at least two diet recalls with a \$10 gift card. These gift cards will be handed out in person at their schools. If participants cannot obtain their gift cards at school, a check will be mailed home to them. Students will also receive \$15 in incentives throughout the study to participate, including a study t-shirt, water bottle and cooking utensils. These incentives will be handed out during TX Sprouts lessons throughout the school year. In addition, students will receive a small toy (\$1) immediately after completing the evaluation measures at baseline and post intervention. In order to get participation in the blood draws, we will offer the child a \$20 cash incentive for each blood draw, which will be given immediately after the draw. We will provide the -screening results to the parents, which will be mailed to the parent, within one month of the test (See Appendix G). We have used these approaches with success in LA Sprouts. Parents will receive \$15 in incentives (groceries, cooking supplies, etc.) at baseline and post-intervention for each completed questionnaire packets (pre- and post-intervention they will be compensated for completing the questionnaire). We will email, text or call parents to remind them to complete and return surveys. The incentives will be distributed to parents during the parental lessons.

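### Only intervention parents have lessons in the comparison year, yet an extra questionnaire route, the only stated incentive delivery and all measured parent data are placed at lessons

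*Protocol*

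**What the plan says.** **When control families have lessons.** Protocol section 4, paragraph on the delayed intervention: "The control schools will receive a delayed intervention (identical intervention as described above) in the year after the post-testing for that wave". The same paragraph adds: "Baseline and post-intervention measurements will occur in the control parents and students within the same time period as the intervention schools".

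**What Aim 2 compares.** Section 3, Hypothesis 2: "TX Sprouts intervention parents compared to control parents will have increased FV intake". It also covers parents' psychosocial variables and the availability of produce at home. All of these come from the parent questionnaire.

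**Routes open to both arms.** Section 4 (TX Sprouts Research Evaluation) has questionnaires handed out or posted, with pre-paid return. Section 6f lets the parent survey come back through the homework folder. Section 8 provides reminders by email, text or phone, with no restriction by arm.

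**What is placed at lessons.**
- Section 4: besides postal return, "parents will also be able to complete the questionnaire at the first and last lessons".
- Section 8, on the $15 given for each completed packet: "The incentives will be distributed to parents during the parental lessons". No other delivery is described.
- Section 5, on parents' measured height, weight, body fat, waist circumference and blood pressure: these "will be collected at first and last family workshop (expecting a subsample only". Section 4 gives the same occasions for height and weight. Section 5 also asks for self-reported height and weight in the questionnaire packet.

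**The concern.** In the year when the arms are compared, a family lesson exists only in intervention schools. Anything done at a lesson is then done in one arm. There are two consequences.

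First, intervention parents who attend have a supervised occasion to fill in a form of about 60 minutes and are paid there. Control parents must return it by post or homework folder, and no way of paying them is stated. Intervention responders may therefore include more lesson attenders, who may also be the parents whose diet changes most. The missing-data methods in section 5 (multiple imputation and full-information maximum likelihood) rest on missingness at random given participants' recorded variables. Lesson attendance could be conditioned on in the intervention arm, if recorded, but has no control counterpart that year.

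Second, the measured parent variables have no control occasion at all, although section 4 promises control-parent measurement in the same period.

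**Working it through.** **1. Routes side by side, comparison year**

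| Element | Intervention | Control |
|---|---|---|
| Questionnaire by hand or post | yes | yes |
| Return by pre-paid post or homework folder | yes | yes |
| Reminders by email, text, phone | yes | yes |
| Self-reported height and weight | yes | yes |
| Completion at first and last lesson | yes | no lesson exists |
| Questionnaire incentive | at lessons | no route stated |
| Measured anthropometry, blood pressure | first and last lesson | no occasion stated |

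The first four rows are balanced. The last three are not. Followed literally, the number of concurrently measured control parents is zero.

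**2. The plan's own parent figures**

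Table 2 gives 12 and 16 schools (alpha 0.05, power 80% and 90%) and 18 and 24 schools (alpha 0.01). Inputs from Table 2: 64 parents per school, difference 0.51 servings per day, ICC 0.071, variance 0.08. Schools per arm:

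k = 2 (z_alpha/2 + z_beta)² (between-school variance + within-school variance / m) / difference²

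Taking 0.08 as the between-school variance, the within-school variance is 0.08 × 0.929 / 0.071 = 1.047, and the school-mean variance is 0.08 + 1.047/64 = 0.0964. Then k = 5.82, 7.79, 8.65 and 11.02. Rounded up and doubled, this is 12, 16, 18 and 24, so all four cells match. The table note calls 0.08 the within-school variance; on that reading k is 0.44 at alpha 0.05 and 80% power, which does not match. That is a separate matter, and the point here does not depend on it.

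**3. Effect of poorer control response on power**

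With 8 schools per arm and 64 parents per school in both arms, SE = √(2 × 0.0964 / 8) = 0.155 and power is 0.91 (normal) or 0.86 (t, 14 df). If control response is halved to 32 per school (assumed), SE = 0.162 and power is 0.88 or 0.83. Loss of power is not the issue.

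**4. Illustration of bias (all inputs assumed)**

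Bias = (difference between arms in the share of more-engaged parents among responders) × (how much better those parents' change is).

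| Share difference | Excess change, serv/d | Bias, serv/d | Share of 0.51 | Two-sided rejection rate with no true effect |
|---|---|---|---|---|
| 0.10 | 0.25 | 0.025 | 5% | 0.053 |
| 0.20 | 0.50 | 0.10 | 20% | 0.099 |
| 0.30 | 1.00 | 0.30 | 59% | 0.49 |

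The last column is Φ(bias/0.155 − 1.96) + Φ(−bias/0.155 − 1.96), in place of 0.05. It applies only if the excess change comes from engagement and not from the lessons themselves.

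**The case against.** The strongest reply is that the questionnaires carry Aim 2 and their main routes are the same in both arms; completion at a lesson is only an added option. This stands. A reader might infer that questionnaire completion is tied to lessons, or that control parents cannot be reminded. The document supports neither.

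Measured parent anthropometry and blood pressure are not in Hypothesis 2 or the parent power calculation. They are planned for a subsample only, and self-reported height and weight exist in both arms. So one cannot infer that Aim 2 lacks a control group. Nor is there a wholesale contradiction with same-period measurement, since the questionnaires can meet that promise. The gap is confined to the measured variables; body fat, waist circumference and blood pressure have no self-report substitute.

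The bias is not demonstrated. An excess change of 0.5 to 1.0 servings per day is about one to two times the whole planned effect, and 59% needs both extremes at once. Control parents who return a long form are also self-selected, and on-site completion may reach parents who would not post one, reducing missingness. All of this stands against quoting a size. It does not remove the asymmetry.

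Control parents might be paid when their lessons begin the following year. The document does not say so, and later payment would still be a different condition at the time of response.

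It is also tempting to extend the point to the children, because of their $15 of items "These incentives will be handed out during TX Sprouts lessons throughout the school year". But most child measures are taken at school in school hours, and the toy at each evaluation and the $20 per blood draw are tied to measurement. The children's primary outcomes are not shown to be affected.

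**Conclusion.** The point holds in limited form. An additional completion route and the only stated delivery of the questionnaire incentive exist in one arm alone during the comparison year. Aim 2 response can therefore depend on arm and on lesson attendance. The likely direction is upward, on the assumption that attenders respond more readily and improve more than other responders. The size cannot be derived from the document, and the 5% to 59% range above is an illustration, not an estimate.

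For the measured parent variables, the statement that control parents are measured in the same period has no means of being carried out, and the passages need to be reconciled. This is a cheap improvement. It does not invalidate Aim 2.

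**What to change.** 1. **Sections 4 and 8.** Collect parent questionnaires and deliver the questionnaire incentives by the same routes (post or homework folder) and in the same weeks in both arms. Record how each form was completed and report parent response by arm.
2. **Sections 4 and 5.** Reconcile the measured parent variables with the delayed-intervention paragraph. Either measure parents at an occasion that exists in both arms, or state that these data are descriptive for the intervention arm only and that between-arm parent BMI is taken from self-report.

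Cost: rewording, some postage or handling, and possibly fewer parent forms from the intervention arm. No larger incentive budget is needed. A measuring occasion in both arms would be new work at 16 schools: the school-event booths in section 6f are described for information and consent signatures, not for measurement. The descriptive option avoids that cost.
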